# A cluster randomised trial to evaluate a physical activity intervention among 3-5 year old children attending long day care services: study protocol

**DOI:** 10.1186/1471-2458-10-534

**Published:** 2010-09-08

## Abstract

**Background:**

Young children are not participating in recommended levels of physical activity and exhibit high levels of sedentary behaviour. Childcare services provide access to large numbers of young children for prolonged periods, yet there is limited experimental evidence regarding the effectiveness of physical activity interventions implemented in this setting. The aim of this study is to assess the effectiveness and acceptability of a multi-component physical activity intervention, delivered by childcare service staff, in increasing the physical activity levels of children attending long day care services.

**Methods/Design:**

The study will employ a cluster randomised controlled trial design. Three hundred children aged between 3-5 years from twenty randomly selected long day care services in the Hunter Region of New South Wales, Australia will be invited to participate in the trial. Ten of the 20 long day care services will be randomly allocated to deliver the intervention with the remaining ten services allocated to a wait list control group. The physical activity intervention will consist of a number of strategies including: delivering structured fundamental movement skill activities, increasing physical activity opportunities, increasing staff role modelling, providing children with a physical activity promoting indoor and outdoor environment and limiting children's small screen recreation and sedentary behaviours. Intervention effectiveness will be measured via child physical activity levels during attendance at long day care. The study also seeks to determine the acceptability and extent of implementation of the intervention by services and their staff participating in the study.

**Discussion:**

The trial will address current gaps in the research evidence base and contribute to the design and delivery of future interventions promoting physical activity for young children in long day care settings.

**Trial registration:**

Australian New Zealand Clinical Trials Registry ACTRN12610000087055

## Background

Regular physical activity among young children can contribute to social, psychological and fundamental motor skill development, maintain bone health and prevent obesity [1-6]. Despite these benefits, research suggests that preschool aged children are not adequately physically active [3,7,8]. For example, a recent study found that 44% and 21% of Australian preschool aged children are not sufficiently active on weekdays and weekends respectively [8].

For a variety of reasons, childcare services (centre based care including long day care services and pre-school) have been identified as a promising setting for the delivery of interventions to increase physical activity among children in early childhood [2,9-12]. First, childcare services provide access to a large and growing number of children for prolonged periods each day [5,13,14]. Second, childcare services have existing infrastructure which can be used to facilitate child physical activity [13]. Third, childcare service staff appear amenable to interventions which aim to enhance children's activity [15,16]. Lastly, descriptive research suggests that service policies and practices and the physical environment of childcare services are important influences on children's physical activity behaviours [9-11,17].

Despite the potential of childcare services as a setting to increase child physical activity, experimental research examining the effectiveness of physical activity interventions in this setting is limited [12,18]. A recent systematic review identified just two randomised controlled trials that aimed to increase children's physical activity levels in childcare[12]. The first, conducted by Alhassan and colleagues [19] reported no change in physical activity levels of Latino children attending a single preschool following an intervention to increase outdoor play time by 60 minutes. The second trial [20], however, found increased physical activity levels among children of one preschool attending classes where staff were trained to integrate movement experiences into the daily indoor programs compared to those attending classes where teachers did not receive training. While such trials provide some evidence regarding the efficacy of specific intervention strategies, the effectiveness of comprehensive, service-level interventions, which are consistent with best practice physical activity guidelines in this setting [2,21] have not been tested.

The aim of this study is to assess the effectiveness and acceptability of a multi-component physical activity intervention, delivered by childcare service staff, in increasing the physical activity levels of children attending long day care services. This paper will describe the study protocol by which this trial will be conducted.

## Methods/Design

### Study Design

The study will employ a cluster randomised controlled trial design (see Figure 1). A sample of eligible long day care services in the study region will be randomly selected and approached to participate in the trial. Ten services will be randomly allocated to a service-level physical activity intervention, delivered over a 15 week period, and ten services will be allocated to a wait list control group. The primary trial outcome measure, mean child step counts per minute, will be collected at baseline and approximately 6 months following baseline data collection. Services allocated to the wait list control group will receive the intervention after the collection of all follow-up data.

**Figure 1 F1:**
[figure not shown]
**CONSORT Flowchart describing progress of participants through the trial**.

The research methods will be reported in accordance with the CONSORT statement [22]. The trial is funded by Hunter New England Population Health, and by a Hunter Medical Research Institute Grant (G0900142). Ethical approval to conduct the study has been obtained from the Hunter New England Area Human Research Ethics Committee (approval No.06/07/26/4.04) and University of Newcastle Human Research Ethics Committee (approval No.20100038).

### Setting

The study will take place in the Newcastle, Lake Macquarie and Port Stephens local government areas of the Hunter Region of New South Wales, Australia. These areas encompass non-metropolitan 'major cities' and 'inner regional' areas as described by the Australian Standard Geographic Classification system [23]. There are 385,376 people residing in the area of which 14,061 are children aged 3 to 5 years [24]. Five percent of residents speak languages other than English and two percent of residents are of Aboriginal or Torres Strait Islander origin [24]. The Hunter Region has lower indices of socio-economic status than the New South Wales state average [23].

### Sample

#### Long day care services

Long day care services in NSW provide centre based care for eight or more hours per day for five days per week and usually enroll children from six weeks old to under six years [14]. These services provide specific preschool programs for children aged three to five years that aim to provide early educational activities to help children prepare for school [14].

There are a total of 85 long day care services in the study region. Twenty of these long day care services (24%) will be recruited into the trial. A list of all long day care services in the region provided by the New South Wales Department of Community Services (the Government Licensing Authority) will serve as the sampling frame. Services catering solely for special needs populations, such as children with vision or hearing impairment, will be excluded from participating in the trial given the specialist care required for such children and the likelihood of a differential effect of the intervention in this population group. To be eligible to participate in the trial long day care services will be required to have at least 25 enrolled children aged three to five years. Eligibility will be confirmed with the Authorised Supervisors (managers) of the services during phone contact as part of the recruitment process.

#### Children

Parents of all eligible children aged three to five years at each of the 20 services will be asked to provide consent for child participation in the study. A minimum of 175 children in each of the intervention and control groups at baseline are expected to participate in the study (average of 18 per service) on the basis of consent rates from similar studies in this setting [19]. Children at the service with a significant physical or intellectual disability will be excluded where this disability prohibits or has the potential to preclude participation in the intervention or impair accuracy of physical activity measures. To be eligible, children must be enrolled to attend the service on the day of the week nominated by the Authorised Supervisor for baseline data collection.

### Recruitment Procedures

#### Long day care services

Prior to formal requests to participate, the research trial will be promoted to Authorised Supervisors through existing childcare networks via a postal newsletter, and an email to all long day care services approximately six weeks and two weeks prior to commencing recruitment respectively.

The order in which eligible services in the study region will be approached to participate in the study will be randomised using a random number feature in Microsoft Excel.

Authorised Supervisors will be mailed recruitment letters informing them of the study and requesting their consent to participate. Consent will be obtained through the supervisor faxing or posting a signed consent form back to the research team. If consent is not received within two weeks a research assistant will telephone Authorised Supervisors to answer any questions they may have and remind them to return their form. Recruitment of services will continue until 20 services consent to participate in the study.

#### Children

To maximise child participation in data collection at participating long day care services, the study will employ strategies recommended for obtaining active parental consent for health research within a school setting [25]. Specifically, the recruitment of participants will include the following components:

##### 1. Recruitment oversight

One member of the research team will act as a designated recruitment coordinator and will be the primary liaison with Authorised Supervisors throughout the study. The coordinator will manage the distribution of consent and information materials to services and parents, and monitor return rates of service and parent consent forms. During the recruitment period, parents and Authorised Supervisors will be able to contact the coordinator directly with any queries about the recruitment. The coordinator will not be involved in the delivery of the intervention or collection of baseline or follow-up measures.

##### 2. Promotion of research prior to requests for participation

The research will be promoted to parents from all participating long day care services via a brochure disseminated a week prior to distribution of information and consent materials.

##### 3. Dissemination of materials to maximise parent engagement

The recruitment coordinator will arrange for recruitment packs (one per parent of each child aged three to five years) to be delivered to each participating service. Distribution of these packs to parents will occur via methods considered appropriate and most effective by the Authorised Supervisor. The research team will aim to hand recruitment packs directly to parents when they drop-off or pick-up their children from the long day care service. This will also enable parents to ask research staff questions about the research. Other distribution methods may include the service emailing parents or placing recruitment packs in children's pigeon holes, lockers or bags. The recruitment packs will be brightly coloured and include an information sheet, consent form and return envelope.

##### 4. Parent reminders

Two weeks after delivery of the recruitment packs, reminder letters will be disseminated via the same channels as described above. The letters will remind parents about the study and the opportunity to participate.

Parents will be asked to sign and return the consent form in the envelope provided to the service their child attends. Parents will have up to three weeks to return their consent form. The consent form includes items that ask for some demographic information about the parent and child, the usual number of days their child attends the service each week, and the after care physical activity and small screen recreation habits of their child on a usual week day. In order to identify any bias due to selective non-participation, all parents will be asked to complete the items on the consent form and return it regardless of whether they consent to study participation.

### Random allocation of long day care services

Services will be allocated to either the intervention or control condition using block randomization performed in a 1:1 ratio in randomly sequenced blocks of two, four or six by a computerized random number function in Microsoft Excel. Allocation of services will be undertaken by a statistician who will have no other involvement in the study, and will occur after all services have been recruited into the trial. As evidence suggests physical activity practices in long day care services differ according to the socio-economic status of the area in which the service is located [26], the random allocation of long day care services will be stratified by the socioeconomic characteristics (high/low) of the service locality. Long day care services with a postcode ranked in the top 50% of New South Wales, based on the Socio-Economic Indexes for Areas [27] will be defined as a 'high socio-economic area service' and those with a postcode ranked in the lower 50% will be defined as a 'low socio-economic area service'. Due to the difficulty in blinding services to their group allocation, this trial will be an 'open' trial. After services have consented to participate in the study a member of the research team not involved in recruitment or data collection will inform services of the group to which they were allocated.

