### Sample size and power calculations

Assuming a step count per minute of 17 among children attending control services and an intra-class correlation of 0.1 [62] a sample size of approximately 280 children (140 per group) attending 20 services at the 6 month follow-up will be sufficient to detect a difference between intervention and control groups of 4 steps per minute with 80% power at the 0.05 significance level. Assuming that long day care services care for 30 children aged three to five years per day on average, a study participation rate of 65% will be required to obtain the desired sample given a 20% attrition rate at the follow-up assessments.

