### Analysis

All statistical analyses will be performed with SAS (version 9.2 or later) statistical software. All statistical tests will be two tailed with an alpha value of 0.5. Descriptive statistics will be performed to describe the demographic and service characteristics of intervention and control groups at baseline. Similarly measures of intervention implementation will be described using descriptive statistics.

The effectiveness of the intervention on child physical activity will be assessed utilising an intention to treat approach. An intention to treat analysis includes all participants in the analysis based on the groups to which they were allocated, without excluding data based on missing outcomes or non-adherence [22]. Specifically, linear mixed models will be used to examine between group differences on the primary trial outcome. Such analyses account for the correlation between pre and post measures and adjust for clustering. Any differences in the characteristics of participants at baseline will be adjusted for in the final linear model.

To ensure the results are robust, a sensitivity analysis will be performed whereby participants' observations at baseline will be used as a substitute for any subsequent missing data. A per-protocol analysis will also be conducted with participants from services which have sufficiently implemented the intervention.

Acceptability of the intervention among staff of services will be assessed by collapsing Likert scale categories and reporting the percentage of staff who responded 'strongly agree' or 'agree' to each acceptability item.

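### Allocation is stratified by area SES, but the stated model does not name the stratum and its covariate rule would rarely bring it in: a low-severity, nearly free improvement

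*Protocol article*

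**What the plan says.** Under Random allocation of long day care services, the article uses "block randomization performed in a 1:1 ratio in randomly sequenced blocks of two, four or six", and "the random allocation of long day care services will be stratified by the socioeconomic characteristics (high/low) of the service locality". The reason given is that "evidence suggests physical activity practices in long day care services differ according to the socio-economic status of the area". High and low are defined by the SEIFA rank of the service's postcode.

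Under Analysis, "linear mixed models will be used to examine between group differences on the primary trial outcome", and "Such analyses account for the correlation between pre and post measures and adjust for clustering". One covariate rule follows: "Any differences in the characteristics of participants at baseline will be adjusted for in the final linear model". The SES stratum is neither named nor excluded.

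Under Sample size and power calculations, the inputs are stated as "Assuming a step count per minute of 17 among children attending control services and an intra-class correlation of 0.1", giving "a sample size of approximately 280 children (140 per group) attending 20 services at the 6 month follow-up". No gain from stratification is claimed there.

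**The concern.** The authors single out area SES in advance as important enough to constrain the randomisation. The stated covariate rule does not suit it, for two reasons. The rule covers characteristics of participants, whereas the stratum is an attribute of the service's postcode. The rule is also triggered by observed imbalance, and stratified blocks are there to prevent imbalance on this factor. The factor chosen beforehand is thus among the least likely to enter the model.

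When allocation is balanced on a prognostic factor, the true variance of the treatment contrast falls. If the factor is left out of the model, its variance stays in the between-service error and the estimated variance does not fall. The interval is then too wide and the test rejects too seldom under the null. With 20 services, the between-service term carries much of the standard error.

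**Working it through.** **Inputs from the article.** 20 services, 10 per arm; 280 children at follow-up, so 14 per service; ICC 0.1; difference 4 steps/min; 80% power; two-sided 0.05. (The Analysis section prints alpha as 0.5, which conflicts with the sample size section; 0.05 is used here.)

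**Inputs assumed.** 5 high-SES and 5 low-SES services per arm; the share *r* of between-service variance explained by SES; pre/post correlations. The article gives none of these.

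**1. The plan's own figure.** Design effect = 1 + (14 − 1) × 0.1 = 2.3. Effective n per arm = 140 / 2.3 = 60.9. No SD is stated, so 280 cannot be reproduced independently. Solving backwards, SD = 4 / (1.960 + 0.842) × √(60.9 / 2) = 7.88 with the normal approximation, or 7.45 with t on 18 df.

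**2. Follow-up data only, baseline ignored.** The true variance of a service mean within arm and stratum is SD² × [0.1(1 − r) + 0.9/14], and the SE of the difference is √(2 × variance / 10). At SD 7.45 and r = 0.25 the bracket is 0.075 + 0.0643 = 0.1393, so the true SE = 7.45 × √(0.2 × 0.1393) = 1.24. The model without the stratum reports 1.343 on average. Simulation of service means (200,000 replicates, SD 7.45; t on 18 df without and 17 df with the stratum) gives:

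| r | Mean SE without / with | Ratio | Type I error without | Power without / with |
|---|---|---|---|---|
| 0 | 1.331 / 1.330 | 1.00 | 5.0% | 80.0% / 79.8% |
| 0.10 | 1.335 / 1.289 | 1.04 | 4.3% | 80.6% / 82.2% |
| 0.25 | 1.343 / 1.225 | 1.10 | 3.3% | 81.3% / 85.9% |
| 0.50 | 1.355 / 1.109 | 1.22 | 1.9% | 83.0% / 91.8% |

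With the stratum, type I error is 5.0% throughout. At SD 7.88 the pattern is the same from a lower start: 75.5% without and 75.2% with at r = 0; 77.9% and 88.6% at r = 0.50. That lower start comes from using t instead of the normal distribution, not from the stratum.

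**3. Using baseline, as the stated model does.** A stable SES difference appears at both waves, so baseline steps absorb much of it. The setting is an effect of 0.51 SD (4 / 7.88), the same SES effect at both waves, and an assumed child-level pre/post correlation of 0.5. Power without / with the stratum, at service level:

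| Analysis | Residual service correlation | r = 0.20 | r = 0.40 |
|---|---|---|---|
| Change from baseline | 0.5 | 80.8% / 80.5% | 86.4% / 86.2% |
| Change from baseline | 0.8 | 93.4% / 93.2% | 95.2% / 95.1% |
| Baseline as covariate | 0.5 | 88.0% / 88.3% | 91.5% / 92.4% |
| Baseline as covariate | 0.8 | 95.4% / 95.3% | 96.9% / 97.0% |

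For the change contrast, type I error is about 5% either way. With baseline as covariate it is 4.4 to 4.8% without the stratum. Correlations as low as 0.3 raise the covariate-adjusted loss to about 3 points, with type I error down to about 4.0%.

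**4. SES matters more at follow-up than at baseline.** Baseline then absorbs less. Under baseline adjustment the loss is about 1 to 5 points and type I error is 3.1 to 4.2%. If SES did not show at baseline at all, the loss would approach the follow-up-only figures in step 2, which serve as a ceiling.

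**The case against.** **The article is condensed.** Covariate lists, including stratification factors, usually sit in the full protocol or SAP, and neither is shown. Silence is not exclusion. This stands: the documents do not show that the stratum will be left out. It does not dispose of the point, because the article does state how covariates enter, and that rule is a poor fit for the stratum.

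**Baseline does most of the work.** Figures that ignore baseline describe a model the article does not use. This largely stands and is why the size is set by steps 3 and 4. A stratum main effect would also leave a group-by-time test essentially unchanged.

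**The stated reason concerns practices, not steps.** The article says that service practices differ by SES and gives no effect on children's step counts. This stands.

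**The stronger reading.** A reader might infer that the standard errors are too large as a matter of fact, and that the trial loses 4 to 9 power points. The documents do not support this. The inference needs SES to predict follow-up steps beyond baseline, which is not quantified, and losses of that size arise only when the baseline measure is ignored. Nor is the planned power breached. In step 2, power without the stratum never falls below its value when SES has no effect; the loss is relative to a stratum-adjusted analysis that the article does not promise.

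**Conclusion.** The point holds in a limited form. The analysis as described does not carry the stratification into the model, and the imbalance-driven rule would seldom do so. If SES is prognostic beyond baseline, inference is mildly conservative: roughly 0 to 5 power points forgone in a baseline-adjusted analysis, usually 0 to 2, and nothing in a change contrast when the SES effect is stable. There is no bias and no inflation of type I error.

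These sizes rest on an assumed even SES split, assumed SES shares and assumed pre/post correlations. The article also does not say whether the mixed model tests a group-by-time term or adjusts follow-up for baseline, which decides where in the range the loss falls. Severity is low: a free improvement, not a flaw that threatens the result.

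**What to change.** Add to the Analysis section, in substance: *The SES stratum (high/low), as used in the randomisation, will be a fixed effect in the primary linear mixed model and in its sensitivity analyses, irrespective of observed baseline balance. If the treatment effect is tested as group-by-time, stratum-by-time will also be included.*

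Apply the same term in the per-protocol analysis. Selecting services by implementation can undo the balance there, so the term then also guards against confounding by SES.

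The cost is about one service-level degree of freedom, or about 0.2 to 0.5 power points if SES turns out not to be prognostic. No data collection is needed, because the stratum must be known for every service before allocation.

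### Disclosure of allocation is tied only to service consent; the plan does not require it to wait for parental consent and baseline measurement

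*Protocol article*

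**What the plan says.** In the protocol article, *Random allocation of long day care services* gives two time points, both at the level of the service. Allocation "will occur after all services have been recruited into the trial". Disclosure is timed as follows: "After services have consented to participate in the study a member of the research team", someone who takes no part in recruiting or measuring, tells them their group. The same section accepts that services cannot be masked: "Due to the difficulty in blinding services to their group allocation, this trial will be an 'open' trial".

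Children are recruited through services that have already joined. *Promotion of research prior to requests for participation* states: "The research will be promoted to parents from all participating long day care services via a brochure". *Dissemination of materials to maximise parent engagement* states: "Distribution of these packs to parents will occur via methods considered appropriate and most effective by the Authorised Supervisor". *Parent reminders* adds: "Parents will have up to three weeks to return their consent form", with forms going back to the service.

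The article also contains safeguards. *Data collection procedures* keeps data collectors blind, asks services not to reveal their group, and tests the blinding by asking collectors to guess. *Recruitment oversight* keeps the recruitment coordinator out of delivery and measurement. *Parent reminders* provides a check on selection: "In order to identify any bias due to selective non-participation, all parents will be asked to complete the items on the consent form", whether or not they consent.

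**The concern.** In a cluster trial, concealing the allocation from the clusters until they have joined protects against selective entry of clusters. It does not protect against selective entry of individuals. If people at the cluster know the arm while individuals are being invited, the two groups can come to differ in who takes part, and randomisation of the clusters no longer guards against that.

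Services here have several ways to affect who is measured and what is measured:

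- The supervisor has a say in how packs and reminders reach parents.
- Under *Sample – Children*, a child is eligible only if enrolled on the weekday that the supervisor nominates for baseline. *Data collection procedures – Physical activity* keeps the same weekday at follow-up.
- The baseline staff survey is self-report, and the Environment and Policy Assessment Observation (EPAO) records staff practices.
- Children's steps on the day depend partly on what staff programme, which is what the intervention sets out to change.

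At stake are the comparability of the two groups of children and the value of the baseline measure as an adjuster.

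**Working it through.** The point concerns the order of steps. The plan states no figure for it, so there is none to reproduce. The check sets the sections side by side.

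**1. What starts the clock for disclosure.** Under *Recruitment Procedures – Long day care services*, service consent is the supervisor's signed form, and recruitment continues until 20 services have consented. Disclosure cannot come before allocation, and allocation waits for all services. The earliest permitted moment is therefore when the twentieth service has consented and the statistician has allocated.

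**2. What still lies ahead at that moment.** The brochure goes to parents of services already participating, one week before the packs. Reminders follow two weeks after the packs, and parents have up to three weeks to return the form. If those three weeks run from delivery of the packs (the text does not say), parental recruitment at a service takes about 1 + 3 = 4 weeks after the brochure. If they run from the reminder, it takes about 1 + 2 + 3 = 6 weeks. For the last service to join, all of this must follow its consent. For services that joined earlier, the text does not say how far parental recruitment will have gone by then.

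**3. Baseline measurement.** *Intervention implementation*, under *Data collection procedures*, sends out the staff survey two weeks before pedometer collection and places the EPAO on the pedometer day. The pedometers are worn by consented children, so that day follows parental consent.

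**4. Whether anything delays disclosure.** The sections on study design, recruitment, allocation, control group and data collection contain no statement that allocation or disclosure waits for the close of parental consent or for baseline. They also contain no statement that disclosure comes before those steps.

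**5. Room for selection.** *Sample size and power calculations* requires 65% participation, so up to 100 − 65 = 35% of families could stay out with the target still met. That leaves room for consent to differ between arms. It does not show that it will.

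**6. What each safeguard covers.**

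| Safeguard | Covers | Leaves open |
|---|---|---|
| Blind data collectors, pedometer count | Fitting and reading of the device | Staff behaviour that day; who consented |
| Coordinator separate from delivery and measurement | Conflict of roles | Not stated to be blind to allocation |
| Items from non-consenting parents | May reveal selection | Does not prevent it; depends on refusers returning the form |
| Independent statistician, allocation after all services join | Selective entry of services | Selective entry of children |

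**The case against.** The strongest reply is that the wording sets only an earliest time. Disclosure after baseline would comply with it fully. A reader might infer that services will be told before parents consent and before baseline; the text does not say so. The participant flowchart (Figure 1), which could settle the order, is not shown in the copy reviewed. This stands, and it limits the point to what the plan permits.

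A reader might also infer that the baseline activity data would be collected unblinded. The article does not support that: data collectors are to be blind, and research staff fit the pedometers and record the counts. What remains is exposure through service staff who may know their arm.

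The service's part in recruitment should not be overstated either. All eligible children's parents are to be asked, the supervisor is not described as choosing children, and the research team aims to hand packs to parents in person. That narrows the route without closing it: in-person delivery is an aim, other channels are allowed, and the supervisor's view governs the method.

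Finally, the *Analysis* section plans a mixed model that uses both measurements and adjusts for baseline differences. A stable difference in who takes part would appear at both times, and the model would absorb part of it. That also stands. It does not cover selection on unmeasured features related to later change, and it is less dependable if staff behaviour has shifted the baseline measure.

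**Conclusion.** The point holds in limited form. Allocation and its disclosure are tied to service recruitment and consent. Within a service, these come before parental consent and baseline, and the plan does not require disclosure to wait. This is more than detail left to a fuller document: the article names a trigger, and the trigger is tied to an event that does not protect the later steps. The existing safeguards limit or may detect the bias but do not prevent it.

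No size can be given. The documents contain nothing on how consent or staff behaviour would shift with knowledge of the arm, and the direction is open as well. The conclusion rests on the visible text. If the flowchart or the full protocol places disclosure after baseline, what remains is to make the text say the same. The change is worth making because it is nearly free and the analysis cannot reliably repair the bias afterwards.

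**What to change.** Replace the disclosure trigger in *Random allocation of long day care services* with a sentence such as: *Services will be informed of their allocation only after parental consent has closed and the baseline pedometer, EPAO and staff survey data have been collected.* Ideally the statistician also generates the allocation only at that point.

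If disclosure has to come earlier for practical reasons, state that whoever recruits parents is blind to allocation, and report consent rates and the characteristics of non-participants by arm.

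The cost is one sentence, plus scheduling staff training after baseline. The stated timetable appears to allow this: follow-up is about six months (roughly 26 weeks) after baseline and the intervention runs for 15 weeks, which leaves about 26 − 15 = 11 weeks for scheduling. If the suggested order is already intended, the change costs nothing.
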